## 5.6 Study Measurements

Treatment Experience Survey. A set of 8 questions asking about a participant's experience using the App (BT-NCBT-00x) will be dispensed on day 80 after enrollment within the App. The survey questions can be seen in Appendix 17.3.

Healthy Days Measure. The standard set of 4-items of the Healthy Days core questions (CDC HRQOL-04) will be dispensed within the App at day 1 and at treatment day 76. The survey questions can be seen in Appendix 17.4.

Net Promoter Score (NPS). Participants will be asked to complete an NPS survey on day 85 within the App. The NPS is a standardized tool for measuring a participant's overall satisfaction with the program. Participants will be asked how likely they are to recommend the app to a friend with a relevant condition and will be asked to enter a number from 1 to 10. The NPS tool can be seen in Appendix 17.5.

*Table 1: Schedule of Assessments*

| Procedures                                              | Pre-enrollment
Screening | Study
Intervention

D1 to D90 | Post-Intervention
Study Visit

D90 to D104 |
|----------------------------------------------------------------|-------------------------------------|--------------------------------------------------|---------------------------------------------------------------|
| Patients identified with a history of NAFLD or NASH            | X                       |                                                  |                                                               |
| Informed consent                                               | X                                   |                                                  |                                                               |
| Labs, biometrics, focused physical exam, BMI                   | X                                   |                                                  | X                                                             |
| Fibroscan >300 db/m                                            | X                                   |                                                  | X                                                             |
| Treatment Orientation Call scheduled                           | X                                   |                                                  |                                                               |
| MRI-PDFF (to be done after Fibroscan)                          | X                       |                                                  | X                                                             |
| Review & confirmation of participant eligibility by PI         | X                                   |                                                  | X                                                             |
| Research staff refers eligible participants using Study Portal | X                                   |                                                  |                                                               |
| AE Reporting                                                   | X                       | X                                    | X                                                 |
| Installation of App & completion of first-time user experience |                                     | X                                    |                                                               |

|                                                                     |  |                                |  |
|---------------------------------------------------------------------|--|--------------------------------|--|
| Study staff contacts patient to schedule post-treatment visit & MRI |  | X                  |  |
| Healthy Days Measure ( HRQOL-04 )                            |  | X 
Day 1 and 76 |  |
| Net Promotor Score                                                  |  | X 
Day 85       |  |
| Treatment Experience Survey                                         |  | X 
Day 80       |  |

X - Patients may be identified during clinic visits, through pre-screening in patient database, or other IRB approved recruitment methods

X - MRI must be completed prior to patient being referred to begin treatment

X - Assess and document serious adverse events

X - Assess and document serious adverse events and adverse events

X - Participant's completion of onboarding and first time user experience marks treatment Day 1

X - This will begin on Day 74

X - Surveys are automatically dispensed to participants in-App on designated days

#### Color Key:

[figure not shown]

= These activities occur during the screening visit

[figure not shown]

= These activities are conducted within the study-App and require no research staff involvement.

## 6. Adverse Event Reporting

### 6.1 Definition of Adverse Events and Serious Adverse Events

AEs will be assessed throughout the study. SAEs will be assessed from the time of signing the informed consent form and AEs will be assessed starting at the time of starting the intervention.

An AE is any untoward medical occurrence in a participant or clinical study participant, temporally associated with the use of study intervention, whether or not considered related to the study intervention. An AE can therefore be any unfavorable and unintended sign (including an abnormal laboratory finding), symptom, or disease (new or exacerbated) temporally associated with the use of study intervention.

### 6.2 Events Meeting the AE Definition

- Any abnormal laboratory test results (e.g., hematology, clinical chemistry, or urinalysis) or other abnormal safety assessments (e.g., ECG, radiological scans, vital signs measurements), that worsen from baseline, and is considered clinically significant in the medical and scientific judgment of the investigator (i.e., not related to progression of underlying disease).

- Exacerbation of a chronic or intermittent pre-existing condition, including either an increase in frequency and/or intensity of the condition.
- New conditions that are identified or diagnosed after the study treatment is administered, even though those conditions may have been present prior the start of the study.
- Signs, symptoms, or the clinical sequelae of a suspected drug-drug interaction.
- Signs, symptoms, or the clinical sequelae of a suspected overdose of a concomitant medication. Overdose per se will not be reported as an AE or SAE, unless it is an intentional overdose taken with possible suicidal/self-harming intent. Such overdoses should be reported regardless of sequelae.
- “Lack of efficacy” or “failure of expected physiological action” per se will not be reported as an AE or SAE. Such instances will be captured in the efficacy assessments. However, the signs, symptoms, and/or clinical sequelae, resulting from lack of efficacy, will be reported as AE or SAE, if they fulfil the definition of an AE or SAE.

### 6.3 Events Not Meeting the AE Definition

- Any clinically significant abnormal laboratory findings or other abnormal safety assessments that are associated with the underlying disease, unless determined by the investigator to be more severe than expected for the participant’s condition.
- The disease/disorder being studied or expected progression, signs, or symptoms of the disease/disorder being studied, unless determined by the investigator to be more severe than expected for the participant’s condition.
- Medical or surgical procedures (e.g., endoscopy, appendectomy): the condition that leads to the procedure is the AE.
- Events in which an untoward medical occurrence did not occur (social and/or convenience admission to a hospital).
- Anticipated day-to-day fluctuations of pre-existing disease(s) or condition(s) present or detected at the start of the study that do not worsen.

If an event is not an AE, as defined above, then it cannot be an SAE even if serious events occur (e.g., hospitalization for signs/symptoms of the disease under study; death resulting from progression of disease).

### 6.4 Events Meeting the Serious Adverse Event (SAE) Definition

- Results in death
- Is life threatening.
  - The term “life-threatening,” in the definition of SAE, refers to the imminent risk of death of a participant at the time of the event. It does not refer to an event,

which hypothetically might have caused death of a participant, if it were more severe.

- Requires inpatient hospitalization or prolongation of existing hospitalization.
  - In general, “hospitalization” means the detainment of a participant at a hospital or emergency ward (usually involving at least an overnight stay) for observation and/or treatment, which would not have been appropriate in a physician’s office or outpatient setting. Complications that occur during a participant’s hospitalization are AEs. If such complications prolong the participant’s hospitalization or fulfills any other SAE criteria, those complications are SAEs. When in doubt as to whether “hospitalization” occurred or was necessary, the AE should be considered serious. If a participant is hospitalized because of an elective treatment, of a preexisting condition that did not worsen from baseline, then the hospitalization is not considered an AE.
- Results in persistent disability/incapacity.
  - The term “disability” means a substantial disruption of a participant’s ability to conduct normal life functions.
  - This definition does not include experiences of relatively minor medical symptoms (e.g., uncomplicated headache; nausea; vomiting; diarrhea; influenza; and accidental trauma [e.g., sprained ankle]) that may interfere with or even prevent daily life functions, but do not constitute a substantial disruption.
- Is a congenital anomaly/birth defect

The Investigator should exercise their medical and/or scientific judgment when deciding whether to report other situations that may cause participants to require medical or surgical treatment (but are not imminently life-threatening or resulting in death or hospitalization) as SAEs. These events should usually be considered serious.

Examples of such events include: invasive or malignant cancers; intensive treatment in an emergency room or at home for allergic bronchospasm; blood dyscrasias or convulsions that do not result in hospitalization; development of drug dependency; or drug abuse.

## 6.5 Adverse Event Severity

The investigator will assess the intensity of each AE or SAE that arises during the course of the study and assign each event one of the following categories:

- **Mild:** The event causes the participant minimal discomfort and does not interfere with the participant’s normal daily activities;
- **Moderate:** The event causes the participant sufficient discomfort to interfere with the participant’s normal daily activities;

- **Severe:** The event causes the participant from performing his or her normal daily activities. Investigators should note that a severe AE assessment should not be confused with an SAE assessment. “Severe” is a category utilized for rating the intensity of an event; both AEs and SAEs can be assessed as being “severe”.

An event is defined as SAE when it meets at least one of the predefined outcomes as described in the definition of an SAE, NOT when it is rated as “severe.”

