### 11.3 Safety Summaries

Treatment-emergent Adverse Events will be summarized using counts and percentages for the participants in the Enrolled Population. A treatment-emergent adverse event (TEAE) will be defined as any AE that occurs after the start of use of the Better Therapeutics App. Summaries of AEs will include:

- All TEAEs;
- Serious TEAEs;
- TEAEs by type of event, severity and relationship to treatment
- and adverse device effects (ADE)

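### The adverse-event severity scale measures only discomfort and daily activities, so symptom-free laboratory, imaging and vital-sign events can only be graded Mild

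*Protocol*

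**What the plan says.** Section 6.5 tells the investigator to "assign each event one of the following categories". There are three:

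- Mild: "The event causes the participant minimal discomfort and does not interfere with the" participant's normal activities.
- Moderate: "The event causes the participant sufficient discomfort to interfere with the" same activities.
- Severe: "The event causes the participant from performing his or her normal daily activities". The sentence is garbled; a verb such as *prevents* was evidently intended.

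The section adds that severity describes intensity and is not the same as seriousness. It gives no criterion based on the size of an abnormality and refers to no other grading scale.

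The AE definition is wider than symptoms. Section 6.1 includes signs, "including an abnormal laboratory finding". Section 6.2 lists "Any abnormal laboratory test results (e.g., hematology, clinical chemistry, or urinalysis) or other abnormal safety assessments", with ECG, radiological scans and vital signs as examples, provided the result worsens from baseline and the investigator judges it clinically significant. Section 6.3 removes findings associated with the underlying disease, unless the investigator considers them worse than expected for that participant.

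Section 11.3 then summarises "TEAEs by type of event, severity and relationship to treatment". The synopsis also lists treatment-emergent AEs (TEAEs) by severity.

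**The concern.** The scale and the events it must grade do not match. A laboratory or vital-sign change can be clinically important without the participant feeling anything, and a scale built on discomfort and daily activities cannot separate a small change of that kind from a large one.

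What is at stake is the meaning of one safety table. Evaluating safety is part of the secondary objective in the synopsis. Section 14 names drops in blood glucose and blood pressure as possible risks in participants with diabetes or hypertension; these are measured quantities and may occur without symptoms. If such events are recorded as Mild because the scale offers nothing else, a reader of the severity table will take the grade as a judgement about the event, when it says only that the participant felt little or nothing.

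**Working it through.** The protocol gives no figure to reproduce and no arithmetic bears on the point. The check is to follow one event through Sections 6.1 to 6.5 and 11.3. Take a laboratory or vital-sign change that causes no discomfort and does not affect the participant's activities.

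1. **Can it be an AE?** Yes. Section 6.1 includes laboratory findings. Section 6.2 requires worsening from baseline and clinical significance, but no symptom.
2. **Does Section 6.3 remove it?** Only if it is associated with the underlying disease and is not worse than expected. A disease-associated finding that remains is therefore an AE because the investigator judged it unusually severe.
3. **Must it be graded?** Yes. Section 6.5 requires one of the three categories for each event.
4. **Moderate?** No. This needs discomfort sufficient to interfere with activities, and there is none.
5. **Severe?** No. However the garbled sentence is repaired, it concerns performing normal activities, and these are unaffected.
6. **Mild?** It is the only category left. If minimal discomfort is read as requiring some discomfort, no category fits and the grade depends on the rater. The scale fails for these events on either reading.
7. **Is the grade reported?** Yes, in the TEAE summary by severity in Section 11.3 and in the synopsis.

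Steps 2 and 6 together show the inconsistency: Section 6.3 treats laboratory findings as more or less severe, while Section 6.5 has no means of saying so. The protocol uses size for laboratory values elsewhere: the exclusion criteria bar ALT or AST above 5 times the upper limit of normal.

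**How many events.** The protocol gives no event rate, so the number cannot be estimated. Table 1 schedules labs and imaging at screening and at Day 90 to Day 104 only, and about 20 participants are planned. For scale, one participant with such an event would be 1/20 = 5% of the Enrolled population used for safety. That is an illustration, not a forecast.

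**The case against.** The strongest reply is that little in the trial depends on this grade.

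- Section 6.3 keeps many ALT and AST changes out of the AE tables, because in NAFLD or NASH they can be attributed to the disease. This stands, and it removes much of what a reader would first think of.
- Medical importance has its own route. Section 6.4 says events that may need treatment should usually be considered serious, and gives blood dyscrasias as an example. Serious TEAEs have their own summary and are reported within 24 hours. This stands. It does not help a clinically significant event that falls short of serious.
- Size is visible elsewhere. Mean change in ALT is an exploratory endpoint analysed by the primary and secondary methods, and Section 11 includes ranges in the summaries of those outcomes. Section 11.3 also tabulates by type of event. This stands for ALT; the severity table itself stays uninformative.
- Section 6.5 says that severity means intensity, so the scale does what it claims. This holds for symptomatic events. For an event with no felt intensity it leaves Mild as a default and gives no assessment.
- The statistical analysis plan, which was not available, might deal with it. It cannot readily do so, because the investigator assigns the grade at the site under the protocol.

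A reader might go further and infer that large liver-enzyme rises in general will be hidden as Mild, or that every laboratory abnormality is graded Mild whatever its size. The documents do not support either. Many such changes never become AEs, ALT is summarised separately, and an abnormality that produces symptoms or limits activities can be graded higher.

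**Conclusion.** The point holds in a limited form. Followed literally, Section 6.5 leaves Mild as the only grade for a symptom-free laboratory, imaging or vital-sign AE that passes Sections 6.2 and 6.3, including one admitted because it was worse than expected. The severity summary then understates it. This is a stated rule that yields a misleading grade, not detail left for later.

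The practical effect is probably small: few events, one table, no change to any efficacy result, and serious events and ALT change still visible elsewhere. The conclusion assumes that such events occur and that investigators apply the definitions as written. Some may grade by clinical judgement instead, but Section 6.5 does not provide for that, and grades would then differ between raters. The change is worth making because it is cheap and must be in place before events are graded.

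**What to change.** Reconcile Sections 6.2, 6.3 and 6.5:

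- Keep the present scale for symptomatic events.
- State in Section 6.5 that laboratory and other measured AEs without symptoms are graded by the size of the abnormality on a named published scale.
- Give the mapping from that scale's grades to Mild, Moderate and Severe, so that Section 11.3 can still use three categories. Say what basis applies to a finding the scale does not cover, such as an imaging change.
- Where an event is both symptomatic and measured, use the higher of the two grades.
- Correct the Severe definition so that it reads as a complete sentence.

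The cost is a short addition to Section 6.5 and a matching note on the AE form. No new tests or visits are needed. The severity table may look slightly less favourable.

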## 6.6 Relationship to Study Intervention

The assessment of causality is one of the criteria used when determining regulatory reporting requirements. The Investigator must use their clinical judgement to assess whether there is a causal relationship between the study treatment and each AE or SAE.

- **Probably Related:** An AE that might be due to the study intervention. The relationship in time is suggestive. An alternative explanation is less likely, e.g., concomitant drug(s), concurrent disease(s).
- **Possibly Related:** An AE that might be due to the study intervention. The relationship in time is reasonable; therefore, a causal relationship cannot be excluded. An alternative explanation is inconclusive, e.g., concomitant drug(s), concurrent disease(s).
- **Not Related:** An AE is not thought to be due to the study intervention.

The Study Investigator should consider and investigate alternative causes (e.g., underlying disease(s); concomitant therapy; and other risk factors), as well as the temporal relationship of the event and study treatment administration, in their assessment of causality. For each AE or SAE, investigators must document, in the medical notes, that they have reviewed the AE or SAE and have provided an assessment of causality. Investigators may change their assessment of causality based on follow-up information.

## 6.7 Serious Adverse Event Reporting

All SAEs shall be reported to the Sponsor or designee within 24 hours of notification of the event. If the investigator receives any updates concerning SAEs, they shall submit such updates to the Sponsor within 24 hours of update receipt. Although the investigator is not required to actively seek out AEs or SAEs after participants have been discharged from the study, if the investigator learns of any study-related SAEs (including death), they must promptly notify the Sponsor of such SAEs.

SAEs will be reported to the Sponsor or designee via secure email. The investigators must also report SAEs to the IRB as required by their IRB regulations.

## 6.8 Following up on Adverse Events

The investigators must follow-up on each device-related SAE by performing or arranging for appropriate supplemental measurements and/or evaluations. This may include performing additional laboratory tests, histopathological examinations, or consulting with other health care professionals.

The CRC or other delegated team member shall record new or updated SAE-related information in a Case Report Form (CRF) hosted in the electronic source.

The investigators will be required to follow-up with each participant involved in AEs and SAEs at each subsequent visit or contact until a resolution or an explanation of the SAEs, or the participant stabilizes, is lost to follow-up, or for up to one week after the participant completes the study in the case of unresolved events.

## 6.9 Adverse Device Effects

An adverse device effect (ADE) is an adverse event related to the use of an investigational medical device. This includes any adverse event resulting from insufficiencies or inadequacies in the instructions for use, the deployment, the implantation, the installation, the operation, or any malfunction of the investigational medical device. This includes any event that is a result of a use error or intentional misuse and any event that has the potential for death or serious injury if the malfunction reoccurred.

Serious ADE definition: an ADE that has resulted in any of the consequences characteristic of a serious adverse event (SAE) that led to:

- 1) death
- 2) fetal distress, fetal death or a congenital abnormality or birth defect or
- 3) a serious deterioration in health that either resulted in
  - a life-threatening illness or injury, or
  - a permanent impairment of a body structure or a body function, or required in-patient hospitalization or prolongation of existing hospitalization, or
  - medical or surgical intervention to prevent life threatening illness or injury or permanent impairment to a body structure or a body function.

## Documenting ADEs

The Study Investigator or other delegated team member shall identify, document, and report any ADE and malfunction resulting in an ADE that occurs any time during the study. After participants have been discharged from the study, if investigators learn of any study-related ADEs, they must promptly notify the Sponsor of such ADEs.

